### 2.7. Outcome assessment and follow-up

As part of the baseline data, we will include information such as age, sex, height, weight, body mass index, coexisting medical conditions (e.g., diabetes and hypertension), diagnosis, total duration of pain, target level of the affected nerve root, and the number of prior epidural injections. For intra-operative information, we will collect the stimulating voltages used during electrical stimulation positioning with 50 and 2 Hz of electrical stimulation, procedure duration, output voltage, impedance, and electric field intensity ([output voltage]2/resistance).

Outcome measures will include: radicular pain intensity; physical functioning; global improvement and satisfaction with treatment; and adverse events. An 11-point NRS (0 = no pain, 10 = unbearable pain) will be used to assess radicular pain intensity; the Korean version 10-item Oswestry disability index (ODI) questionnaire (range: 0–100; 0 = no disablility) will be used to assess physical function; global perceived effect according to the 7-point Likert scale will be used to assess patient satisfaction and improvement; and adverse events during treatment and follow-up will be individually recorded.

The primary outcome will be NRS and ODI at 1, 2, and 3 months after the procedure. The reduction in pain intensity and decrease in ODI compared with baseline. Complications that occur during the procedure will be reported, if present, and adverse events will be further evaluated during the monthly follow-up visits.

### 2.8. Statistical analysis

The intention-to-treat analysis will be applied, and the data of every randomized subject will be analyzed each month, regardless of lost to follow-up or withdrawal from the study. Follow-up loss or withdrawal from the study will be considered treatment failure. Because we expect possible treatment failure during the 3-month follow-up period, linear mixed model will be used to analyze the secondary continuous variables. Adjustments will be made for the baseline values to 0 to compare the decrements of the secondary outcomes at 3 months. The categorical variables will be presented as absolute numbers and percentage. The continuous variables will be presented as the mean with standard deviation, 95% confidence interval, or median and interquartile range. To compare the demographic data of the 2 groups, the chi-square or Fischer exact tests will be used to assess categorical variables and the unpaired *t* test or Mann–Whitney *U* test will be used to analyze continuous variables. *P* values <.05 will be considered statistically significant. All statistical analyses will be performed using SPSS 26.0 (IBM Corp., Chicago, IL).

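### The mixed model is assigned to secondary continuous variables, but the only continuous outcomes, NRS and ODI, are primary and have no named between-group analysis

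*Protocol article*

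**What the plan says.** Section 2.7 (Outcome assessment and follow-up) lists the outcomes: "Outcome measures will include: radicular pain intensity; physical functioning; global improvement and satisfaction with treatment; and adverse events". It then names the primary one: "The primary outcome will be NRS and ODI at 1, 2, and 3 months after the procedure". The next sentence has no verb and no primary or secondary label: "The reduction in pain intensity and decrease in ODI compared with baseline". Two outcomes remain. One is a patient rating: "global perceived effect according to the 7-point Likert scale will be used to assess patient satisfaction and improvement". The other is safety, where the plan is only that "adverse events during treatment and follow-up will be individually recorded". The word secondary does not appear in this section.

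Section 2.8 (Statistical analysis) states that a "linear mixed model will be used to analyze the secondary continuous variables". Its baseline adjustment, which sets baseline to 0 and compares the falls at 3 months, is likewise directed at secondary outcomes. The chi-square, Fisher, t and Mann-Whitney tests are introduced by the words "To compare the demographic data of the 2 groups". What remains in 2.8 is general: intention-to-treat, monthly analysis of all randomized patients, losses counted as treatment failures, descriptive summaries and the 5% threshold.

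**The concern.** The analysis section fixes its one model for follow-up data on a class of outcomes that the outcome section does not contain. It gives no between-group method to the class that the outcome section calls primary.

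At stake is which result answers the trial's question. With NRS and ODI each measured at three visits, one could report an overall group effect, a group-by-visit interaction, a month-3 contrast or separate monthly comparisons. These answer different questions, and with 10 patients per arm (20 / 2) they can lead to different conclusions. The wording of 2.8 leans two ways: it speaks of analysing the data every month, and also of a comparison at 3 months.

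**Working it through.** No figure in the protocol needs to be reproduced here. The check sets each outcome or measurement in 2.7 against each analysis sentence in 2.8.

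| Item in 2.7 | Type | Role in 2.7 | Between-group method named in 2.8 |
|---|---|---|---|
| NRS at 1, 2, 3 months | numeric, repeated, has a baseline | primary | none |
| ODI at 1, 2, 3 months | numeric, repeated, has a baseline | primary | none |
| Global perceived effect | ordinal, 7 points, a rating of change | not labelled | none that fits |
| Adverse events | individual events | not labelled | none |
| Intra-operative measures | continuous | not an outcome | none |

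Counts: outcomes labelled secondary, 0; continuous outcomes other than the primary ones, 0; primary outcomes with a named between-group method, 0 of 2. NRS has 11 points and is called continuous here by the usual convention.

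Four readings could give the model a target or the primary outcome a method:

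1. *Global perceived effect is the secondary continuous variable.* It is an ordinal rating of perceived change. It has no pre-treatment value to set to 0 and cannot show a fall from baseline.
2. *The intra-operative measures are meant.* They are continuous ("For intra-operative information, we will collect the stimulating voltages used during electrical stimulation positioning"), but they are recorded during the procedure, are not listed among the outcomes and have no 3-month value.
3. *The verbless sentence on change from baseline is a secondary outcome that lost its label.* This is possible, and it would give the model a target. It would still leave NRS and ODI at months 1, 2 and 3, the stated primary outcome, without a named test.
4. *Counting losses as treatment failures supplies the primary analysis.* No success or failure endpoint is defined, so this rule names no comparison.

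The remaining reading is that the word secondary in 2.8 is a slip and that the model was meant for NRS and ODI. Only these two have both a baseline and repeated follow-up, so only they can show the fall from baseline that 2.8 describes. Even then, 2.8 does not say whether the monthly results or the 3-month comparison carries the primary conclusion, nor how two primary outcomes are to be judged at one 5% level.

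**The case against.** The strongest reply is that the intention is evident. No outcome is explicitly called secondary, so the set is empty only by elimination. The description of the model fits NRS and ODI and nothing else. On that reading 2.8 already gives a model family, a time point, a treatment of baseline, an analysis population and a threshold, and the defect is one wrong word. This largely stands and is why the point is not graded higher. It does not remove the conflict, because the text still names no contrast for the primary conclusion, and a later plan would have to depart from it to be usable.

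A second reply is that this is a condensed article and a full analysis plan may name the primary test. That would answer a complaint about silence. Here, however, the article does assign its model, and to a class of outcomes that its own outcome section lacks.

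Two stronger inferences are tempting, and the document supports neither. A reader might infer that the primary method will be chosen after the data are seen. A condensed article cannot show this, since the method may be prespecified elsewhere. A reader might also put a figure on the inflated false-positive rate from testing two scales at three visits. That figure depends on correlations between visits and scales that the protocol does not give, and multiplicity is a separate issue that does not measure the harm of a mislabelled model.

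**Conclusion.** The conflict between 2.7 and 2.8 is real. Taken literally, the mixed model has no suitable outcome and 0 of the 2 primary outcomes have a named between-group analysis. The most likely explanation is a wrong label, with NRS and ODI as the intended targets. This rests on the article's text alone, on treating NRS and ODI as continuous, and on treating the 7-point rating as ordinal.

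No numerical effect on the trial's error rate is claimed. The point should be fixed, but it is not critical: this is a 20-patient pilot intended as a basis for later trials, the intended reading can be guessed, and the repair is mainly one of wording.

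**What to change.** In section 2.8:

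- State that the linear mixed model analyses the primary NRS and ODI, with group, visit (1, 2 and 3 months), group-by-visit and the baseline score as a covariate. The covariate replaces setting baseline to 0. Subtracting baseline forces a slope of 1 between baseline and follow-up, whereas a covariate lets the data set the slope and deals better with chance imbalance between arms of 10.
- Name the between-group contrast that carries the primary conclusion. Month 3 is the natural candidate, since 2.8 already uses it.
- Say how the two primary outcomes share the 5% level. Examples are an equal split (0.05 / 2 = 0.025 each), a fixed testing order, or a requirement that both succeed. Alternatively, declare the pilot's tests exploratory.
- Analyse global perceived effect by a rank or ordinal method.

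In section 2.7, align the primary-outcome sentence with the chosen contrast. Complete or delete the verbless sentence on change from baseline, and label the remaining outcomes as secondary.

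The cost is a few sentences across the two sections. No new data are needed: the months stay the same, and baseline scores are already implied by the planned comparison with baseline. The software already named can fit the model.

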**Methods/design::**

This study will be a prospective, double-blind randomized controlled pilot study. In this study, total 20 patients will be recruited and distributed equally into 2 groups: high-voltage (60V) PRF, low-voltage (45V) PRF. Outcomes will be radicular pain intensity; physical functioning; global improvement and satisfaction with treatment; and adverse events. The assessments will be performed at the 3-month follow-up period after the end of the treatments. The findings will be analyzed statistically considering a 5% significance level (*P* ≤ .05).

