### 2.2. Trial design

As a part of the ethical approval process, we will provide a written informed consent form to the participants before their enrollment in the study. This study will be a double blind, randomized controlled trial to compare the 2 groups (1:1). This study will be performed in 20 participants with LRP and conducted on outpatients visiting the pain clinic of International St. Mary’s Hospital, Catholic Kwandong University. The clinical trial and the items to be examined in this study are presented in Figure 1.

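### Zeroing baseline makes the NRS and ODI analysis a change-score comparison, not a baseline adjustment; baseline should be a covariate, for a gain that is usually real but of unknown size

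*Protocol article*

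**What the plan says.** Section 2.8 (Statistical analysis) states that a "linear mixed model will be used to analyze the secondary continuous variables", and then: "Adjustments will be made for the baseline values to 0 to compare the decrements of the secondary outcomes at 3 months". Section 2.7 (Outcome assessment and follow-up) describes the outcome in the same terms: "The reduction in pain intensity and decrease in ODI compared with baseline". Neither section names baseline as a covariate.

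Section 2.8 speaks of secondary outcomes, but Section 2.7 says: "The primary outcome will be NRS and ODI at 1, 2, and 3 months after the procedure". The other patient-rated scale, global perceived effect, has no baseline value. The sentence on baseline can therefore only apply to NRS and ODI, which are the trial's main outcomes.

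**The concern.** The sentence calls the step an adjustment, but subtracting the baseline fixes the baseline slope at 1 instead of estimating it. Patients enter on a high NRS (Section 2.3 requires at least 5, Section 2.4 excludes scores above 9), so some regression to the mean is expected and the true slope is probably below 1. A change score then over-corrects: the arm that happens to start higher tends to show the larger fall, whatever the voltage does.

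Randomisation makes this average out over repeated trials, but a single trial with 10 per arm can carry a sizeable gap. What is at stake is precision in a small trial, and an estimate that still depends on chance imbalance when the data to remove that dependence are already collected.

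**Working it through.** The article states no power, SD, effect size or correlation, so there is no figure of its own to reproduce.

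**Inputs from the article.** "total 20 patients will be recruited and distributed equally into 2 groups" (Abstract, Methods/design), with 1:1 allocation in Section 2.2, gives 10 per arm. The significance level is 5% ("values <.05 will be considered statistically significant", Section 2.8), taken as two-sided. Entry NRS is 5 to 9 (Sections 2.3 and 2.4). No entry limits are set on ODI.

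**Assumed inputs.** The correlation r between baseline and follow-up is 0.3, 0.5 or 0.7. The SDs are as given below.

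**1. Chance imbalance.** The SE of the baseline difference is sqrt(2/10) = 0.447 SD. A gap above 0.5 SD in either direction means |Z| > 0.5/0.447 = 1.118, with probability 0.26. With equal SDs the change score carries (1 - r) times the gap into the estimate. At r = 0.5, a gap of 0.5 SD shifts it by 0.25 SD.

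**2. Precision at one visit, equal SDs (s).** Var(change) = 2(1 - r)s². Var(baseline as covariate) = (1 - r²)s². The ratio is (1 + r)/2. Estimating the slope with N = 20 multiplies the covariate variance by 1 + 1/(N - 4) = 17/16.

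| r | (1 + r)/2 | × 17/16 | Variance reduction | Change-score 95% CI wider by |
|---|---|---|---|---|
| 0.3 | 0.65 | 0.69 | 31% | 20% |
| 0.5 | 0.75 | 0.80 | 20% | 12% |
| 0.7 | 0.85 | 0.90 | 10% | 5% |

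Break-even is where (1 + r)/2 × 17/16 = 1, so r = 32/17 - 1 = 0.88. Above that the covariate no longer pays for itself.

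**3. NRS with restricted entry.** Assume an SD of 2 at both times before selection, and let V0 be the baseline variance after selection. The covariate variance is 4(1 - r²) × 17/16. The change-score variance is 4(1 - r²) + (1 - r)²V0. Take V0 = 1.68, which is a normal distribution centred on 7 with SD 2, cut at 4.5 and 9.5 so that whole scores run from 5 to 9.

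| r before selection | Change score | Covariate | Variance reduction |
|---|---|---|---|
| 0.3 | 3.64 + 0.49 × 1.68 = 4.46 | 3.87 | 13% |
| 0.5 | 3.00 + 0.25 × 1.68 = 3.42 | 3.19 | 7% |
| 0.7 | 2.04 + 0.09 × 1.68 = 2.19 | 2.17 | 1% |

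A sharper cut at exactly 5 and 9 gives V0 = 1.165, and reductions of about 8%, 3% and -1% from the same formulas.

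**4. Where the gain reverses.** With k the ratio of baseline SD to follow-up SD, the large-sample loss from the change score is (k - r)² in units of follow-up variance. It vanishes at k = r, where the baseline slope is 1 and scores do not regress to the mean. The 17/16 factor then leaves the covariate analysis about 6% worse in variance.

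**5. A zeroed baseline row, if it were kept as a response.** Let V be the variance of each change score. A random-intercept model with one common variance pools three visits with variance V and one with variance 0, giving (3V + 0)/4 = 0.75V. The SE of the direct month-3 difference is then sqrt(0.75) = 0.866 of its true value, about 13% too small. Simulation under compound symmetry (40,000 null trials, 10 per arm) gave ratios of 0.865 to 0.868 and type I error of about 9%. With the row dropped, the ratio was 1.00 and type I error 5%.

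**The case against.** The strongest reply is that nothing here is invalid. Change from baseline is the outcome that Section 2.7 declares, the comparison is unbiased under randomisation, regression to the mean acts on both arms equally in expectation, and chance imbalance is already reflected in the SE. This is a pilot, and for NRS the gain may be close to nothing. All of this stands, and it limits the point to precision and conditional imbalance. It does not remove it: the covariate costs almost nothing, and ODI has no entry range that would directly shrink the gain.

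A second reply is that analysis detail belongs in a fuller document. That would cover an omission. Here the article fixes a method and calls it an adjustment.

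Two stronger readings are tempting and are not supported. A reader might infer that P values will be too small because a zero-variance baseline visit enters the mixed model. The article does not say that the row is kept, names no covariance structure, and does not say which contrast is tested; its outcome visits are months 1, 2 and 3. Even with the row kept, the group-by-visit contrast has the correct SE and 5% type I error under compound symmetry. A reader might also apply the equal-SD gains of 10% to 31% to NRS, but the entry criteria narrow its baseline spread.

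**Conclusion.** The point holds as a recommended change in analysis. Section 2.8 specifies a change-score comparison under the name of adjustment, for the outcomes that matter most. The estimate is not biased.

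The loss of precision depends on correlations and SDs that the article does not give. A variance reduction of 10% to 31% is plausible where baseline and follow-up spread are similar, as may hold for ODI. About 1% to 13% is plausible for NRS under the assumed entry distribution, less with a sharper cut, and the sign turns by up to about 6% if scores do not regress to the mean. That there is usually a gain is well founded; its size is not.

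The understated SE from a retained zero row is a conditional risk only. It needs the row to be kept, a common-variance structure and a direct month-3 contrast together.

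**What to change.** Replace the sentence in Section 2.8 with: *Baseline NRS (or ODI) is a covariate in the linear mixed model; the response contains only months 1, 2 and 3; the group difference at each visit is reported with a 95% CI.*

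Apply it to NRS and ODI by name, since Section 2.7 calls them primary, and apply it whatever any baseline test shows. Decrements can still be reported: once baseline is in the model, the group contrast is the same for change and for final score. The wording also excludes a zeroed baseline row from the responses.

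The cost is one sentence and one degree of freedom. Baseline NRS and ODI are already needed for the declared outcome, so no new data are required.
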